#### Secondary outcome measures

The safety of the probiotic formulaThe change between groups in the following biomarkers or measurements from baseline to 12 weeks:(i)HbA1c(ii)insulin sensitivity indices, including Matsuda-ISI [16] and homeostatic model assessment-IR [17](iii)fasting plasma lipids, such as triglycerides, free fatty acids, total cholesterol, HDL-c and LDL-c(iv)plasma zonulin and lipopolysaccharide(v)hs-CRP(vi)gastrointestinal symptoms(vii)body mass index, waist circumference, and waist and hip ratio(viii)blood pressure(ix)faecal microbial and metabolomics profiles.

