#### Statistical analysis

Analysis will be conducted using the intention-to-treat principle and missing data will be imputed with baseline values for a conservative estimate (i.e. no change). Descriptive statistics will be presented as mean ± standard deviation, or median with range, as appropriate. Primary and secondary outcomes will be analyzed using generalized linear models. The following covariates will be added to the model: sex, age and percentage weight change. Additionally, if there is an imbalance between the groups of prediabetes and type 2 diabetes mellitus, this will be included as a covariate in the model. Three planned subgroup analyses will be completed between participants who are taking metformin, participants classified as prediabetic or type 2 diabetes mellitus and participants defined as compliant. Chi–square analysis will determine associations between categorical variables.

For the gut microbiome analysis, sequenced data will be interpreted using the bioinformatics tools programmed in the Ion Reporter™ software. Quantitative Insights Into Microbial Ecology (QIIME) algorithms will determine the bacterial diversity within a sample (alpha diversity) and between all the samples (beta diversity). Additionally, multivariate data analysis with principal component analysis on the diversity indexes and comparisons of genus and species level data will be performed to reveal differences in the microbial composition between the two groups. Differences in relative abundance of taxa between the intervention and placebo group and between participants receiving and not receiving metformin will be determined using ANOVA, using subject as a blocking factor. Changes in relative abundance will be tested for correlations with patient biochemical measurements. For all statistical tests, the Benjamini–Hochberg false discovery rate adjustment [20] will be used to account for the number of taxa tested in each comparison.

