## Discussion

This randomized trial will assess the efficacy and safety of a multi-species probiotic formulation in the management of prediabetes and type 2 diabetes mellitus metabolic markers. The study outcomes may lead to novel treatments to reduce the metabolic disturbances associated with these disorders. This study will also provide empirical evidence to address currently unresolved issues with the efficacy and safety of probiotics. In designing this clinical study, several key decisions were made to overcome current limitations in the published literature and reduce possible biases.

While focusing on those with prediabetes, subjects with early type 2 diabetes mellitus were included to assess the feasibility of inducing partial or complete remission of type 2 diabetes mellitus. This decision also meant including participants taking metformin as this drug is commonly prescribed early in type 2 diabetes mellitus; it has also been shown to have effects on the microbiome [21, 22]. Furthermore, microbiota-based interventions may reduce gastrointestinal symptoms associated with metformin administration with a consequent improvement in medication compliance [23]. As far as we are aware, the interaction between the gastrointestinal microbiota, probiotics and metformin has not been explored in patients with prediabetes and type 2 diabetes mellitus. Therefore, this study will assess the efficacy and safety of a novel multi-species probiotic and provide preliminary data on its effect on metformin.

Limitations of the study include the short-term impact of the intervention, as subjects will be treated for only 12 weeks. Additionally, the small number of visits during the study can be considered a risk factor for non-compliance. Moreover, it must be remembered this study is investigating the short-term impact of a multi-species probiotic formulation to help improve fasting blood glucose levels. It is known that probiotics do not recolonize the intestinal tract but rather are transient colonizers and that wash-out of administered doses can take from approximately 4–6 weeks, thereby leading to a therapy that may be not be permanent.

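### The metformin comparison of taxa names no diabetes term, so a disease difference can be reported as a metformin difference

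*Protocol article*

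**What the plan says.** All references are to the Protocol article.

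- **Taxa contrast** (Statistical analysis, second paragraph). Differences in relative abundance are tested between the arms and also "between participants receiving and not receiving metformin will be determined using ANOVA", with subject as the blocking factor. A Benjamini–Hochberg adjustment covers the number of taxa. No other model term is named.
- **General model** (same section, first paragraph). "Primary and secondary outcomes will be analyzed using generalized linear models", with sex, age and percentage weight change as covariates. Diabetes status enters conditionally: "if there is an imbalance between the groups of prediabetes and type 2 diabetes mellitus, this will be included as a covariate in the model".
- **Subgroups** (same paragraph). "Three planned subgroup analyses will be completed between participants who are taking metformin"; diabetes status and compliance are the other two. They are listed side by side and not crossed.
- **Why metformin users are in the trial** (Discussion). After explaining why early type 2 diabetes was admitted, the text continues: "This decision also meant including participants taking metformin as this drug is commonly prescribed early in type 2 diabetes mellitus". It adds that metformin itself affects the microbiome, and that the interplay of microbiota, probiotics and metformin is unexplored in these patients.
- **Eligibility** (Inclusion criteria). The treatment criterion allows metformin alongside diet for any participant, not only those with diabetes.
- **Samples** (Stool samples). Each participant gives stool at baseline and at 12 weeks.

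**The concern.** Metformin use is observed, not allocated. The protocol links disease status to the exposure, because metformin is common in early type 2 diabetes. It also links disease status to the outcome, because the Abstract and Background associate gut microbiome changes with type 2 diabetes. A factor tied to both can confound a comparison of users with non-users, and the sentence that defines the comparison does not adjust for it. The Benjamini–Hochberg step limits chance findings across taxa; it does nothing about confounding.

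At stake is the meaning of the metformin results. A taxon that differs between prediabetes and diabetes, or changes differently over 12 weeks, could be listed as differing by metformin. The Discussion also presents the trial as a source of early information on the probiotic and metformin together. A user-versus-non-user difference does not address that question, and nor do separate subgroup results.

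**Working it through.** **Plan's own figure.** The protocol gives no number for this contrast. Its one computable figure, 32 participants for fasting glucose, reproduces: 2 × (1.960 + 0.842)² × 2.0²/2.0² = 15.7, so 16 per arm and 32 in total. Nothing below depends on it.

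**Step 1. How much of a disease difference leaks through.** Let *q* be the share with type 2 diabetes, *a* the metformin share among them and *b* the metformin share in prediabetes. If metformin has no effect, the unadjusted user-minus-non-user difference equals the disease difference multiplied by

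P(T2D | user) − P(T2D | non-user) = *qa*/[*qa* + (1−*q*)*b*] − *q*(1−*a*)/[1 − *qa* − (1−*q*)*b*].

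The documents give none of *q*, *a*, *b*; all values are assumptions.

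| *q* | *a* | *b* | T2D among users | T2D among non-users | Leak |
|---|---|---|---|---|---|
| 0.5 | 0.6 | 0 | 0.30/0.30 = 1.00 | 0.20/0.70 = 0.29 | 0.71 |
| 0.5 | 0.6 | 0.10 | 0.30/0.35 = 0.86 | 0.20/0.65 = 0.31 | 0.55 |
| 0.5 | 0.8 | 0.05 | 0.40/0.425 = 0.94 | 0.10/0.575 = 0.17 | 0.77 |
| 0.3 | 0.6 | 0.05 | 0.18/0.215 = 0.84 | 0.12/0.785 = 0.15 | 0.68 |
| 0.5 | 0.4 | 0.4 | 0.20/0.40 = 0.50 | 0.30/0.60 = 0.50 | 0 |

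The first four rows give 55–77%. They are combinations taken from the ranges, not every corner. The most extreme corner (*q* = 0.3, *a* = 0.8, *b* = 0) gives 1 − 0.06/0.76 = 0.92.

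**Step 2. Effect on a test.** Simulation: 60 participants, two samples each, true metformin effect zero, 3,000 runs per row, one taxon at nominal two-sided 5% before any multiplicity adjustment. The disease difference is assumed to be 0.8 SD, either constant over time (level contrast) or in the 12-week change (change contrast).

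| *q*, *a*, *b* | Level: false difference | Rejects, without → with diabetes term | Change: false difference | Rejects, without → with diabetes term |
|---|---|---|---|---|
| 0.5, 0.6, 0 | 0.57 SD | 57.7% → 5.4% | 0.58 SD | 49.2% → 5.2% |
| 0.5, 0.6, 0.10 | 0.45 SD | 40.5% → 4.6% | 0.45 SD | 33.6% → 5.4% |
| 0.5, 0.8, 0.05 | 0.61 SD | 71.5% → 4.6% | 0.62 SD | 61.3% → 4.9% |
| 0.3, 0.6, 0.05 | 0.55 SD | 45.3% → 5.4% | 0.55 SD | 37.8% → 4.9% |
| 0.5, 0.4, 0.4 | 0.01 SD | 5.0% → 4.8% | 0.00 SD | 4.1% → 4.4% |

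If the disease difference is constant and change is compared, it cancels: the unadjusted test rejects about 5% of the time in every row.

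**Step 3. What blocking on subject does.** Take 60 subjects, two samples each, and metformin use that does not change within a subject. With subject as fixed blocks the design matrix has rank 60. Adding metformin leaves it at 60, so the metformin main effect is not estimable. Subject plus time has rank 61, and adding metformin-by-time gives 62, so only that term can be estimated. If metformin is instead tested against between-subject variation, it is estimable, and the level columns of Step 2 apply.

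**Step 4. Does the conditional covariate reach this contrast?** It is stated for the generalized linear models, one paragraph before the ANOVA. Its trigger reads most naturally as imbalance of disease status between the arms. The arms can be perfectly balanced while nearly every metformin user has diabetes. Read instead as unequal numbers with prediabetes and diabetes, it would not fire at *q* = 0.5, where the leak is 0.55–0.77 in the three unequal-use rows. Neither trigger tracks the association between metformin and disease.

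**The case against.** **Blocking on subject.** As fixed blocks, it absorbs any constant difference between prediabetes and diabetes. This stands, and it rules out the stronger reading that a disease difference *will* be reported as a metformin effect. It does not clear the plan: under that reading the stated user-versus-non-user comparison cannot be produced, and the term that can be, metformin-by-time, is not named and stays open to differential change by disease.

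**No shares are given, and anyone may take metformin.** A reader might infer that users are essentially the diabetes group and non-users the prediabetes group. The Discussion says only that the drug is common in early type 2 diabetes, and the inclusion criteria do not confine it to diabetes. Overlap is likely but not documented, and with equal use there is no bias.

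**The covariate may apply.** Secondary outcomes include "faecal microbial and metabolomics profiles", so one can argue that the generalized linear models and their covariate extend to taxa. The ANOVA sentence does not say so, and the trigger would still be the wrong one.

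**Some of this belongs in an analysis plan.** Fair for interaction tests within subgroups; listing two overlapping subgroups separately is not an error. The Discussion's remark on probiotics and metformin describes a field of interest and defines no estimand, so it would be too strong to say that the protocol breaks a promise. For the taxa contrast, however, the article itself fixes the comparison, the test, the blocking factor and the multiplicity rule.

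**It is exploratory, in a 60-person pilot.** True, and this limits the weight of the point.

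**Conclusion.** The point holds in a limited form. The taxa comparison by metformin use is non-randomised, names no diabetes term, and is not clearly covered by the conditional covariate. If metformin use differs by disease status, a disease difference (or, for change, a different 12-week course) can appear as a metformin difference. Under the four assumed combinations of unequal use, 55–77% of it passes into an unadjusted between-participant contrast. At an assumed 0.8 SD, this gives false rejection in about 41–72% of level tests and 34–61% of change tests, against about 5% with a diabetes term. These sizes rest wholly on assumed shares and effects; equal use gives no bias.

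Separately, the blocking statement leaves the metformin main effect inestimable if subject is a fixed block. Certain misattribution is not supported, and nothing here touches the randomised fasting glucose comparison.

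**What to change.** Change the taxa paragraph of Statistical analysis as follows.

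1. Compare metformin users and non-users with diabetes status in the model or, alternatively, within type 2 diabetes participants only. For change over 12 weeks, include diabetes status by time (equivalently, diabetes status as a covariate for the change score).
2. State how subject enters: as a random effect, or by analysing each participant's change. Name the metformin term being tested.
3. Label the result an exploratory association.
4. To address the probiotic–metformin question in the Discussion, also report the treatment-by-metformin interaction with its confidence interval, adjusted for diabetes status, as exploratory.

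Cost: wording only, since metformin use and diabetes status are already recorded. The price is a wider interval. At *q* = 0.5 and *a* = 0.6, the 60 participants include 30 with diabetes, so a comparison within diabetes has 30 × 0.6 = 18 users against 12 non-users before drop-out; at *a* = 0.8 it has 24 against 6. The interaction will be imprecise for the same reason, which is why it should be read from its interval and not from a significance test.

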## Methods

### Design

This pilot study is a single site, randomized, double-blind, placebo-controlled clinical trial conducted at the Charles Perkins Centre Royal Prince Alfred Clinic in Sydney, Australia. Sixty adults with prediabetes or early type 2 diabetes mellitus will be randomized to take either a multi-species probiotic capsule or placebo for 12 weeks. The Standard Protocol Items: Recommendations for Interventional Trials (SPIRIT) was used to elaborate the study protocol (see Additional file 1). Participants’ progression through the trial is presented in Fig. 1 (CONSORT diagram [14]).

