#### Stool samples

Stool samples will be collected at baseline and 12 weeks using a stool specimen collection kit. This collection kit includes an instruction booklet for the stool sample collection and transportation, ice packs, gloves, a sterile container, sealed plastic pouch, cool box and an AnaeroGen™ Compact sachet, which preserves the microbiological characteristics of the sample for 72 hours. Participants will bring the stool sample to the clinic and the containers will be stored at 4 °C and analyzed by matrix-assisted laser desorption ionization time-of-flight mass spectrometry 24–48 hours after collection. In addition, a 1 g sample will be stored at −80 °C for faecal microbial and metabolite profiling. DNA extraction will be performed using the QIAamp DNA stool kit (Qiagen, Sydney, NSW, Australia). Faecal microbial composition will be identified by sequencing the 16S rRNA using the Ion S5 next-generation sequencing system (Thermo Fisher, Sydney, NSW, Australia). Short-chain fatty acids, secondary bile acids and choline by-products will be measured using gas chromatography-mass spectrometry.

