### Data analysis and statistical considerations

#### Sample size

As this is a pilot study, no evidence about blood glucose differences is available for this product. Therefore, it was decided to use the number of participants needed to detect a mean difference between the groups in fasting plasma glucose level of 2.0 mmol/l (standard deviation 2.0 mmol/l) at week 12 with 80% power and 95% confidence as a starting point. The number of subjects needed is 32. The fact that the study includes two different cohorts (participants with prediabetes and early type 2 diabetes mellitus) was also taken into consideration, as owing to the lack of stratification at randomization the variance could be high. Therefore, the sample size has been inflated to 30 per group (including a drop-out rate of 25%) to give a total sample size of 60 eligible participants.

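### The taxa ANOVA blocks on subject but names only between-subject contrasts; group-by-visit, the contrast that matches the endpoint, is not named

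*Protocol article*

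**What the plan says.** The Statistical analysis section names two comparisons: "Differences in relative abundance of taxa between the intervention and placebo group and between participants receiving and not receiving metformin". It says that these "will be determined using ANOVA, using subject as a blocking factor". It does not say whether subject is fixed or random, and it names no visit term and no group-by-visit term. Change enters only in the following sentence, and only for correlations: "Changes in relative abundance will be tested for correlations with patient biochemical measurements". The Benjamini–Hochberg adjustment is then applied over the taxa in each comparison.

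Three other places bear on this:

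- **Design:** participants "will be randomized to take either a multi-species probiotic capsule or placebo for 12 weeks", so each subject is in one arm throughout.
- **Stool samples:** "Stool samples will be collected at baseline and 12 weeks", so there are two samples per subject.
- **Secondary outcome measures:** faecal microbial profile (item ix) is in the list of outcomes defined as the between-group change from baseline to week 12.

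Metformin is a permitted background treatment under Inclusion criteria and is not randomized.

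**The concern.** A blocking factor removes the variation between blocks. When the block is the subject, that is the variation that carries a comparison between arms, or between users and non-users of a background drug. The sentence therefore pairs two contrasts with a model term that absorbs both.

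The outcome is secondary, but it matters to the trial. The Background hypothesizes that a shift in the gut microbiome produces the metabolic benefit, and the Discussion presents the interplay of microbiota, probiotic and metformin as something not yet explored. As worded, the sentence leaves several analyses open: one with no group test, one with a diluted effect, one with the wrong error term, and the right one. They would give different lists of taxa, and the choice could be made after the data are seen. The false discovery rate step does not help, because it needs valid p-values as input.

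**Working it through.** **Inputs.** There are 60 subjects, 30 per group (Sample size), with 2 stool samples each (Stool samples) and arm constant within subject (Design). Assumptions: metformin use is constant within subject, with a balanced split for illustration only; all samples are present. The plan gives no figure of its own for this analysis. Its one computed figure, 32 subjects for fasting glucose, reproduces as 2 × (1.96 + 0.84)² × (2.0/2.0)² ≈ 15.7, so 16 per arm and 32 in total. It plays no part here.

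**1. Fixed subject blocks.** An effect has degrees of freedom only if adding it raises the rank of the design matrix (120 rows).

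| Terms in the model | Rank |
|---|---|
| subject | 60 |
| subject + group | 60 |
| subject + group + metformin | 60 |
| subject + visit | 61 |
| subject + visit + group-by-visit | 62 |
| as above + metformin-by-visit | 63 |

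Group and metformin main effects each add 60 − 60 = 0. Group-by-visit adds 62 − 61 = 1 and leaves 120 − 62 = 58 residual degrees of freedom. With week-12 samples only, 60 rows and rank 60 leave 0 residual degrees of freedom.

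**2. What group-by-visit estimates.** In a simulated data set of this shape, the group-by-visit coefficient from the fixed-block model was 0.8298. The between-arm difference in mean change was also 0.8298. This is the contrast defined under Secondary outcome measures.

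**3. Random subject.** The group main effect is now estimable. With complete pairs it compares subject means over both visits. Randomization makes the expected baseline difference 0. If the week-12 difference is D, the expected main effect is (0 + D)/2 = D/2.

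**4. Main effect tested against the within-subject residual.** Let ρ be the correlation between a subject's two samples. The true variance of the contrast exceeds the one used by the factor (1 + ρ)/(1 − ρ). With 58 degrees of freedom the two-sided 5% critical value is 2.002, so the actual type I error is P(|t₅₈| > 2.002/√[(1 + ρ)/(1 − ρ)]). The documents give no ρ, so a range is shown.

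| Assumed ρ | Variance factor | Effective cut-off | Type I error |
|---|---|---|---|
| 0.3 | 1.86 | 1.469 | 15% |
| 0.5 | 3.00 | 1.156 | 25% |
| 0.7 | 5.67 | 0.841 | 40% |
| 0.8 | 9.00 | 0.667 | 51% |

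A simulation of 4,000 runs at ρ = 0.5 gave 24.95%.

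**5. The two candidate treatment tests.** With equal variances at the two visits, the variance of the arm difference is proportional to 2(1 − ρ) for change and to 1 − ρ² = (1 − ρ)(1 + ρ) for baseline-adjusted week 12. Since 1 + ρ < 2 for ρ < 1, the second is smaller. At ρ = 0.5 the values are 1.00 and 0.75. They are different estimators.

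**The case against.** The strongest reply is that blocking on subject is an ordinary way to handle baseline and week-12 pairs. On that reading group-by-visit was meant, and it is estimable. The article states neither fixed nor random subjects, and a condensed article may leave visit terms and error strata to a fuller document that is not shown.

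Much of this stands. A reader might infer from the wording that the treatment effect on taxa cannot be estimated at all. The documents do not support that: two samples per subject make group-by-visit estimable, and a random subject effect, which the text does not exclude, makes the main effects estimable too. A reader might also infer that the reported p-values will rest on the wrong error term. Nothing in the article says how the sums of squares or error strata will be set, so the error rates in step 4 show what one possible implementation would do, not what is planned.

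The reply does not clear the sentence. It does more than omit detail: it fixes a model term and names two contrasts, and the contrasts are plain between-group differences with no visit or change. The random-subject reading does not deliver the listed endpoint either, because the main effect averages in a pre-treatment sample. Metformin is the clearer case. If the aim is a difference in level between users and non-users, fixed subject blocks cannot give it, and metformin-by-visit answers a different question.

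One further criticism should be left out. The article does not say that abundances will be analysed untransformed, so a log-ratio transformation is an option and not part of this error.

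**Conclusion.** The point holds as a mis-specified secondary analysis of moderate severity. With fixed subject blocks, the arm and metformin main effects named in the plan each have 0 degrees of freedom. With random subjects, the arm main effect is diluted by about half. The contrast that matches the plan's own endpoint, group-by-visit, is available with 58 residual degrees of freedom but is not named.

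The rank result for arm follows from the parallel-group design alone. The result for metformin assumes that use does not change during the 12 weeks. The halving assumes complete pairs and balance at baseline in expectation. The primary outcome (fasting plasma glucose, analysed by generalized linear models) and the sample size are unaffected.

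**What to change.** Replace the ANOVA sentence with a statement of contrast and error term for each comparison.

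- **Treatment.** For each taxon, choose one of these in advance: (a) week-12 abundance compared between arms with adjustment for baseline abundance (ANCOVA, usually the more precise), or (b) the group-by-visit term in a model with subject effects. The two can give different answers, so the plan should not leave both open.
- **Metformin.** Test differences in level between users and non-users as a between-subject comparison against between-subject error, for example on the baseline samples or as a main effect with subject random. If the question is whether change differs by metformin use, state metformin-by-visit as a separate question.
- **Multiplicity.** Apply the Benjamini–Hochberg step to the p-values from these tests, per comparison, as already planned.

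The cost is a revised sentence and the matching code, settled before unblinding. No new samples or visits are needed.
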